##### Implementation

We evaluate the implementation of ROAR (acceptability, adoption, retention, and engagement), service outcomes (service intensity) and client outcomes (overdose, return to substance use, and quality of life). All outcomes will be presented as a percentage of the women who consent to participate in ROAR, except for acceptability (in which the denominator will be eligible inmates with documented moderate to severe OUD at pre-screening), and quality of life (which is a continuous measure). Outcomes measured at months three and six (retention, self-reported overdose, return to substance use, and quality of life) will be compared over time to determine if the likelihood of these events changes as participants are in the community for a longer period. We will compare these longitudinal outcomes measured as proportions using a McNemar’s test. Since quality of life at baseline as well as months three and six will be measured, repeated measures Analysis of Variance will be used to assess change over time.

We will assess the association of baseline characteristics with implementation and client outcomes using both descriptive statistics as well as bivariate methods. Bivariate methods will be selected as appropriate for each variable; they may include but are not limited to chi-squared tests, fisher’s exact, t-test, Mann-Whitney U, Pearson’s and Spearman’s correlation coefficients, etc.

Qualitative data will be entered into NVivo qualitative software and coded by two research staff using an iterative codebook created by the research team. . This method will be conducted via group process, with reliabilty checks conducted by the lead qualitative researcher ([name]).. These processes will continue until patterns and inferences are well articulated. Qualitative findings will be triangulated with quantitative data collected for Aim 2 to support and explain intervention effectiveness, by providing evidence related to intervention acceptability and feasibility; implementation quality, intensity, and barriers; and contextual influences.

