**Fig. 1 Fig1:**
[figure not shown]
Conceptual model for ROAR pilot evaluation

Aim 1 collects participant survey data, completes qualitative interview data, and abstracts medical charts to assess: 1) Implementation Outcomes, 2) Service Outcomes, and 3) Client Outcomes. Implementation outcomes examine acceptability, adoption, engagement and retention in the ROAR pilot. Aim 2 evaluates the effects of the ROAR program on our primary outcome of any opioid overdose. This is a binary outcome indicating a fatal or non-fatal opioid-related overdose event in the 6 months following release from incarceration.

#### Aim 1

Pilot the ROAR intervention to reduce risk of overdose among adult women released from prison. ROAR is offered to all eligible female inmates being released to one of Oregon’s four most populated counties over the 18-month recruitment period. The pilot (*n* = 100) includes a process evaluation using quantitative and qualitative measures grounded in the Consolidated Framework for Implementation Research (Keith, Crosson, O'Malley, Cromp, & Taylor, 2017). Baseline participant surveys assess history of overdose, lifetime mental health status and current depression using the Patient Health Questionnaire-9 (PHQ-9). Three-month and 6-month followup surveys of participants assess self-reported return to opioid use, non-fatal opioid overdose and engagement with SUD treatment and recovery support services. Qualitative interviews with participants, CRMs, and clinicians assess barriers and facilitators to retention in treatment and acceptability of the intervention.

#### Aim 2

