### ROAR intervention

The pre-release phase includes screening and medication initiation activities, which are briefly described below. The post-release phase includes survey and interview data collection and regular participant check-ins, along with community treatment and ongoing support from CRMs. Return to opioid use is an expected part of the recovery process, and all participants are released with nasal naloxone rescue kits. The naloxone kits are reviewed with the participants during the health services visit, at day of release with the CRM, and throughout their follow up in community to assess the need for ongoing education, training, and whether or not the naloxone has been used and there is need for an additional rescue kit. Nasal naloxone is a medication that cannot be abused and has no “street value” in terms of the being sold or traded in community, therefore, there is limited risk of it being sold or stolen. Participants who return to opioid use remain eligible to continue participation in ROAR, to receive support from their CRM, and are contacted for participation in the 3-month and 6-month follow-up interviews. All study procedures and assessments are summarized in Table 2. Note that variation in the timeline is expected, based on changes in participant release dates. If a participant receives an injection of XR-NTX more than 3 weeks prior to release (due to unexpected change in release date), then the participant will be maintained on XR-NTX with monthly injections up to the week prior to actual release.

**Table 2 Tab2:** ROAR Assessments and Study Activities

	Pre-Release ROAR Activities								Release Day	Post-Release ROAR Evaluation Visits						
Tests/ Procedures	Prescreen		Consent & Baseline	CRM Reach In Visits			Health Services			2 Week Check In	1 Month Check In	2 Month Check In	3 Month Follow Up (& Qualitative Interview)	4 Month Check In	5 Month Check In	6 Month Follow Up
**Study Visit Number**	**PS1**	**PS2**	**Consent & Baseline Interview**	**CRM1**	**CRM 2**	**CRM 3** **(optional)**	**HS1**	**HS2**	**V0**	**V1**	**V2**	**V3**	**V4**	**V5**	**V6**	**V7**
**Approximate Weeks Post-Release**	**−12**	**−8**	**−6**	**−4**	**−2**	**−1**	**−4**	**−1**	**0**	**2**	**4**	**8**	**12**	**16**	**20**	**24**
Medical Chart Review	**X**															
Prescreen Interview (DSM-5 OUD)		**X**														
Inclusion/Exclusion Checklist		**X**														
Demographics (Informed Consent and Consent Quiz)			**X**													

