 XR-NTX is not indicated for pregnant or nursing women, so a pregnancy test is administered in corrections health services prior to injection. A new positive pregnancy test prior to release would be a serious adverse event. The ROAR nursing staff would communicate the result to the Health Services Manager, who woulddetermine appropriate procedures, in line with Department of Corrections policies and in compliance with PREA.

 Immediately prior to the injection, participants again review the risks and benefits of the medication with nursing staff, including a potential increased risk of overdose if a dose is missed or after stopping treatment. If no opioid withdrawal symptoms are present, a single 380 mg XR-NTX dose is administered intramuscularly to the right upper outer gluteus by a trained corrections health services nurse. Additional training on XR-NTX and nasal naloxone is provided to the ROAR study team by the study clinicians. The injection site and any side effects are assessed during the final week of incarceration as needed.

Consented ROAR participants who do not receive an XR-NTX injection for any reason may choose to continue in the ROAR evaluation, and remain eligible for services provided by the CRM and facilitated entry into community SUD treatment.

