##### Participant retention and compensation

Retention is a vital part of any intervention protocol and being able to contact a participant is instrumental to high retention rates. Thus, it is critical to have each participant complete a locator form and update the form as needed throughout the pilot intervention and evaluation. The locator form is initially completed immediately following informed consent, and participants are queried for any changes during each follow up activity. When completing the locator form, participants provide their names and any aliases, current address, email address, and telephone numbers for themselves and (if possible) at least two other people. C At time of consent, participants are provided a ROAR contact card that includes the name, email address and cell phone number for research staff that will complete the follow-up check-ins and interviews. Participants are also reminded that CRMs can share their contact information with research staff. This is important because CRMs complete reach-in appointments close to date of release when participants may have additional contact information and often meet participants on their day of release. Research staff and CRMs communicate frequently about updated participant contact information.

Barriers to retention in the ROAR pilot are similar to barriers to retention in SUD treatment programs and include return to opioid use, transportation costs, competing resources, mistrust of medical providers and research staff, fear of stigma, and concerns about the medication and potential side effects. Frequent contact with the CRM likely increases study retention. Connections to the CRM provide participants with opportunities to clarify processes, and reduce uncertainty or fears about participation in the pilot program.

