### Data collection and measures

Our primary outcome is any opioid overdose (fatal or non-fatal) within 6 months following release from incarceration. This is a binary outcome indicating a fatal or non-fatal opioid-related overdose event in the 6 months following release from incarceration. We identify fatal opioid overdose with linked vital statistics data and define fatal overdose using International Classification of Disease, 10th Revision specific codes for opioid poisoning. Non-fatal overdose is measured using Oregon Medicaid and hospitalization discharge data. We use the date of admission as the overdose date. Emergency department encounters occurring within 1 day of a hospitalization are not counted as distinct overdose events. As secondary analyses, we will examine which baseline characteristics are associated with implementation and client outcomes using both descriptive statistics as well as bivariate methods.

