#### Follow-up Surveys

At 3- and 6-months post-release, participants are invited to complete a 30-minute face to face survey that collects information about medical status, employment/support status, alcohol and drug use, overdose experiences, family/social relationships, psychiatric status and mental health treatment, patient health questionnaire responses, quality of life, criminal justice involvement, treatment services review, and MOUD treatment adherence. The ROAR research coordinator records participant responses directly in REDCap. The survey meetings are conducted in person in a public place of the participant’s choosing.

Items include the ASI-Lite questions adapted for a 3-month timeframe and the overdose experience items. Quality of life is measured using the World Health Organization Quality of Life-8 . Items using previously tested language will capture overdose experience. Participants are compensated 25 USD for completing the 3-month survey and 50 USD for completing the 6-month survey. Information collected from surveys is not shared with law enforcement officials.

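### The month-3 versus month-6 overdose comparison uses paired self-report, so deaths and women missing a survey drop out; the resulting bias can run either way, and the linked overdose records that would avoid it are not analysed by time since release

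*Protocol article*

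**What the plan says.** The Implementation part of the Analysis section takes retention, self-reported overdose, return to substance use and quality of life at months 3 and 6. It says they "will be compared over time to determine if the likelihood of these events changes as participants are in the community for a longer period". For the outcomes that are proportions it fixes the test: "We will compare these longitudinal outcomes measured as proportions using a McNemar’s test".

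Aim 1 shows what the surveys record: "Three-month and 6-month followup surveys of participants assess self-reported return to opioid use, non-fatal opioid overdose". Follow-up Surveys gives the recall window only in part: "Items include the ASI-Lite questions adapted for a 3-month timeframe and the overdose experience items".

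On loss, the retention section states: "Barriers to retention in the ROAR pilot are similar to barriers to retention in SUD treatment programs and include return to opioid use". Against that, the ROAR intervention section states: "Participants who return to opioid use remain eligible to continue participation in ROAR", and such women are still contacted for both follow-up interviews.

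A source that needs no survey exists. Data collection and measures says "We identify fatal opioid overdose with linked vital statistics data", takes non-fatal events from Medicaid and discharge data, and dates them by admission. Consent to linkage with state data is an inclusion criterion. These records feed the between-group primary model and an exploratory regression on baseline characteristics. The primary model has terms for ROAR participation, covariates and county, and none for time since release.

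**The concern.** The question is whether overdose becomes more or less likely as women spend longer in the community. It matters to this programme: before the injection, women are told of risks "including a potential increased risk of overdose if a dose is missed or after stopping treatment", and continuing medication after release is optional.

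The chosen data cannot answer it cleanly, for two reasons. First, a fatal overdose can never be self-reported, so the gravest form of the outcome is excluded by construction. Second, McNemar's test uses only women with a value at both times. If relapse makes women harder to retain, those who overdosed are over-represented among the missing pairs, and the comparison rests on a selected group. A reader could then take a flat, falling or steeply rising result as a finding about risk when it partly reflects who answered.

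**Working it through.** **The plan's own figure.** The only loss figure is interim retention among the first 42 women injected: (31 + 5)/42 = 85.7%, which reproduces the stated 86%. Only 5 of these women had completed month 6, so this is not a month-6 survey response rate. It is borrowed below as a plausible value.

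**Inputs.**
- Period risks: the power section's 20% to 25% per year is about 5% to 6.25% per 3 months. Assumed here: p1 = 4% early and p2 = 8% late (a true doubling), and separately a constant 6%.
- Fatal share f = 2/17 = 11.8%, from the 2 fatal and 15 non-fatal overdoses of 283 quoted in the Background (assumed to be separate women in one study). s = 1 − f = 0.882.
- Chance that a surviving woman completes both surveys: r0 = 0.86 with no overdose, rE after an early non-fatal overdose only, rL after a late one only, and the lower of rE and rL after both. The values 0.50 and 0.70 are assumptions; the article gives none.
- Overdoses in the two periods are taken as independent, with 3-month recall windows.

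**Formula.** Weights of the completed pairs:
- both periods: p1·s·p2·s·min(rE, rL)
- early only: p1·s·(1 − p2)·rE
- late only: (1 − p1)·p2·s·rL
- neither: (1 − p1)·(1 − p2)·r0

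Observed ratio = (both + late only)/(both + early only).

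**Worked case** (rE = 0.86, rL = 0.50): both 0.0012, early only 0.0279, late only 0.0339, neither 0.7596, total 0.8226. Observed early risk is 0.0292/0.8226 = 3.5% and late risk 0.0351/0.8226 = 4.3%, a ratio of 1.20.

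| Selective loss | rE | rL | Early seen | Late seen | Ratio (true 2.0) |
|---|---|---|---|---|---|
| none | 0.86 | 0.86 | 3.5% | 7.1% | 2.01 |
| equal | 0.50 | 0.50 | 2.2% | 4.3% | 2.01 |
| equal | 0.70 | 0.70 | 2.9% | 5.9% | 2.01 |
| late only | 0.86 | 0.50 | 3.5% | 4.3% | 1.20 |
| late only | 0.86 | 0.70 | 3.5% | 5.9% | 1.66 |
| early more | 0.50 | 0.70 | 2.1% | 5.9% | 2.8 |

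With a constant true risk of 6%, the ratio is 1.00 under equal loss, 0.59 or 0.82 when only late-overdose women are lost selectively (rL = 0.50 or 0.70), and 1.38 when early-overdose women are lost more (0.50 against 0.70).

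**How much loss hides a rise completely?** Observed late risk = p(1 − q)/[p(1 − q) + (1 − p)(1 − r)], where q and r are the shares without a month-6 survey among women with and without a late overdose. For a rise from 5% to 10% with overall loss of 14.3% and no selective loss of early-overdose women, q = 57.1% and r = 9.5% give 0.0429/(0.0429 + 0.8145) = 5.0%, exactly flat. Deaths alone (q = 2/17, r = 0) give 0.0882/(0.0882 + 0.9) = 8.9%, so deaths by themselves would not hide a doubling.

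**Power.** Exact two-sided McNemar at 5%, for 5% against 10%: 19% with 100 complete pairs, 15% with 86. A real rise would often look flat even with no selective loss.

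**The case against.** **The strongest case against** is that this is a secondary, within-group comparison, openly described as self-reported, in a condensed article whose analysis plan is not shown. Fatal overdoses are captured in the primary outcome, and women who relapse stay eligible and are contacted. All of this stands and limits the weight of the point. It does not remove it, because the article itself fixes the question, the data source and the test.

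**A reader might infer that the loss is one-sided, so that the test must hide a late rise.** The documents do not support that. Women who die or are lost before month 3, and women who overdose early and then miss month 6, leave the pairs too. The Background places elevated drug-related death in the first 4 weeks after release. Under equal selective loss the ratio is unbiased.

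**A reader might also infer that the comparison conceals harm once the opioid block ends.** One injection blocks for up to 1 month, so months 2 and 3 are already past it and lie in the early period. Women may also continue or switch medication. Month 3 against month 6 does not separate blocked from unblocked time.

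**Linked records have faults of their own.** They miss overdoses that never reach care, and every participant leaves with naloxone. The article quotes sensitivity of 97% and specificity of 85%. If these applied per woman and period, which it does not say, a true 4% and 8% would read as 0.04 × 0.97 + 0.96 × 0.15 = 18.3% and 0.08 × 0.97 + 0.92 × 0.15 = 21.6%, a ratio of 1.18. Events stay few: about 4 + 8 = 12 in 100 women under the assumed doubling. The linked comparison is therefore an addition, not a replacement.

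**Conclusion.** The point holds in limited form. The comparison excludes fatal overdose by construction and rests on women who completed both surveys, while the article gives a reason to expect that completion depends on the outcome. Neither the direction nor the size of the bias can be fixed from the documents. Under the stated assumptions a true doubling could appear as anything from about 1.2 to 2.8, with no bias if early- and late-overdose women are lost equally. Most of the distortion would come from selective survey loss rather than from deaths.

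The article contains no other analysis by time since release; whether a separate analysis plan does cannot be judged here. The primary 6-month comparison is not affected. The change is worth making, but the study's main conclusion does not depend on it.

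**What to change.** In the Implementation analysis, add a within-ROAR comparison of fatal plus non-fatal opioid overdose by time since release, months 0-3 against months 4-6, optionally showing month 1 separately. Use the dated Medicaid, discharge and vital-statistics records already linked, with the person-time rules of the Opioid Overdose analysis (stop at death, leave out re-incarceration). Report rates and a rate ratio with confidence intervals that allow for two periods per woman, and call the result descriptive because events will be few.

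Keep McNemar's test, labelled as self-reported non-fatal overdose among women who completed both surveys. Beside it, report deaths and survey non-response by period.

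The cost is some wording and one further model on data in hand, with no new visits or data requests. State two limits with the result: linked records miss overdoses that never reached care, and imperfect specificity can pull the ratio towards 1.

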#### Target population

We plan to enroll 100 women in the ROAR pilot intervention during the approximately18-month recruitment period (June 2019 through December 2020). Approximately 60 adult females are released each month, half of whom are released to the four pilot counties. We expect that at least 40% will have histories of opioid abuse, providing a pool of about 12 women eligible for participation monthly, or about 3 per week. To facilitate recruitment, the Oregon Department of Corrections Office of Research, Data, & Government Efficiencies generated a list of female adults in custody who meet the following criteria: 1) have a release date during the 18-month recruitment period, 2) are being released to the four target counties, and 3) have a documented SUD. This initial list generated 2 months prior to the project launch included a total of 235 potential participants. Characteristics of the original ROAR recruitment pool are included in Table 1.

**Table 1 Tab1:** Characteristics of ROAR Participant Recruitment Pool, March 2019, *N* = 235

	N (%)		N (%)
**Age Group**:		**Offense Type:**	
31 to 45	124 (52.8%)	Property	114 (48.5%)
25 to 30	54 (23.0%)	Person	69 (29.4%)
46 to 60	35 (14.9%)	Statute	52 (22.1%)
18 to 24	19 (8.1%)		
61 and Up	3 (1.3%)		
**Race/Ethnicity**:		**Drug Offense:**	
White	182 (77.4%)	None	158 (67.2%)
Black	26 (11.1%)	Some Drug Offenses	54 (23.0%)
Hispanic	16 (6.8%)	Only Drug Offenses	23 (9.8%)
American Indian	7 (1.3%)		
Asian	3 (1.3%)		
Pacific Islander	1 (0.4%)		

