Locator Form			**X**													
Medical Status			**X**													
Baseline Overdose			**X**													
Baseline Psychiatric Status/Mental Health Treatment			**X**													
PHQ-9			**X**													
Liver Function Test							**X**									
Pregnancy Test and Birth Control Assessment								**X**								
Naloxone Challenge Log								**X**								
Clinical Opiate Withdrawal Scale								**X**								
XR-NTX Injection Log								**X**								
Injection Site Abnormality Log								**X**								
Follow Up Locator Form										**X**	**X**	**X**	**X**		**X**	**X**
Follow-up Medical Status													**X**			**X**
Employment / Support Status													**X**			**X**
Alcohol and Drug Use													**X**			**X**
Follow-up Overdose													**X**			**X**
Family/Social Relationships													**X**			**X**
Follow-up Psychiatric Status/Mental Health Treatment													**X**			**X**
Follow-up PHQ-9													**X**			**X**
World Health Organization Quality of Life-8													**X**			**X**
Pregnancy & Birth Control													**X**			**X**
Criminal Justice													**X**			**X**
Treatment Services Review													**X**			**X**
MOUD Treatment Adherence & Satisfaction													**X**			**X**
Qualitative interview (if randomly chosen)													**X**			
CRM Reach-In Log				**X**	**X**	**X**	**X**	**X**	**X**	**X**	**X**	**X**	**X**	**X**	**X**	**X**

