**Fig. 3 Fig3:**
[figure not shown]
Preliminary ROAR enrollment: first 7 months of 18-month recruitment cycle (2/10/2020)

Early recruitment and retention rates suggest the that ROAR pilot will successfully enroll and retain participants as planned. Of 150 adults in custody referred for prescreening interview by end of month 7, 93% were screened using an in-person interview guide. Table 3 summarizes reasons why 32 women in custody were excluded from pre-screening interview process. Of those who completed the pre-screen interview (n=140), 61 were eligible to enroll. At total of 51participants (84% of those eligible at pre-screen) were consented and enrolled into the pilot. Of the first 46 participants released from prison, 42 accepted the first injection of XR-NTX prior to release. Of those, 86% were retained as participants in community (31 still active, and 5 completed 6-month follow-up). Recruitment is planned for a total of 18 months.

**Table 3 Tab3:** Ineligibility for ROAR Pilot Project (First 7 Months Recruitment)

	Number
**Reasons ineligible for pre-screening, post administrative record review (multiple response)**	32
Detainers	14
Mental Health	10
Medical Concerns	6
Refused prior to being presented with information sheet	5
Special Housing	2
Change in Release Date	1
**Reasons Ineligible for Consent/Baseline, post Screening Interview (multiple response)**	79
Does not meet DSM-5 criteria for moderate to severe opioid use disorder	68
Not interested in obtaining treatment to cut back or quit opioid use or to prevent using opioids when released	68
Would not consider medication-based treatment for opioid use disorder	36
Not willing to take at least one evidence-based measure to avoid becoming pregnant	11
Chronic pain that requires ongoing treatment with opioid pain medicine	7
Release outside of target counties	5
Disqualified by prison health services	2
Planning on conceiving in the coming months	1

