#### Baseline Surveys and Assessments

During the informed consent/baseline data collection visit with the ROAR staff, participants are asked to complete baseline surveys, which provide individual characteristics that will be used to describe study participants and explore factors potentially associated with implementation and client outcomes. The Baseline Survey collects demographic information, medical status, overdose experiences, psychiatric status and mental health treatment, and PHQ-9 responses. Selected items from the Addiction Severity Index Lite (ASI Lite) will assess an individual’s history related to substance use, family/social status, employment, and medical and psychosocial issues.

*Questionnaires Included in Baseline Survey:*PHQ-9Participant DemographicsASI Lite (selected items)

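### Quality of life is assigned to repeated-measures ANOVA, which in its classical form drops every woman with a missed survey; this wastes data and can bias the change over time, in either direction

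*Protocol article*

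**What the plan says.** **Method.** In the protocol article, under Analysis, Implementation, the only analysis named for change in quality of life is: "repeated measures Analysis of Variance will be used to assess change over time". The same sentence gives its premise: "Since quality of life at baseline as well as months three and six will be measured". The section gives no rule for women who miss a survey.

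**Expected loss.** The section on participant retention and compensation states: "Barriers to retention in the ROAR pilot are similar to barriers to retention in SUD treatment programs and include return to opioid use". It lists other barriers as well, such as transport costs, mistrust and stigma, and adds that women with adverse reactions or a poor experience of clinical staff may leave more often. On the other side, the ROAR intervention section says: "Participants who return to opioid use remain eligible to continue participation in ROAR". Such women are still contacted for both follow-up interviews.

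**Observed loss.** Among 42 women who accepted the injection before release, the section on preliminary enrollment and retention data reports: "Of those, 86% were retained as participants in community (31 still active, and 5 completed 6-month follow-up").

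**Occasions.** In Table 2 the row "World Health Organization Quality of Life-8" carries two marks, in the positions used by the other 3- and 6-month items, and none at consent and baseline. The baseline section reads: "The Baseline Survey collects demographic information, medical status, overdose experiences, psychiatric status and mental health treatment, and PHQ-9 responses". Quality of life is not among these. The WHOQOL-8 is listed only among the 3- and 6-month questionnaires.

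**The concern.** Classical repeated-measures ANOVA needs a complete row for each woman, so a woman who answers one survey and misses another contributes nothing. If everyone who misses a survey does so by chance, only precision is lost. The article gives reason to expect something else: return to opioid use is named as a cause of loss, and it is plausibly tied to quality of life. If women are lost because their score was low at one visit, those who remain were selected partly for a high score at that visit. Their scores at the other visits then lie closer to the mean. The difference between visits is a selection effect that the ANOVA would report as change. At stake is the interpretation of one client outcome of the pilot. The overdose analysis is not affected.

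**Working it through.** **1. The article's own figure.** (31 + 5)/42 = 85.7%, which matches the reported 86%, so about 14% were lost. Only 5 women had reached month 6, so final loss could be higher; 28-30% is used as a second, assumed level.

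**2. Inputs not in the documents (assumed).** Score SD 1; true change zero; 90 women at month 3 (of the 100 planned); correlation 0.6 between months 3 and 6; odds of missing month 6 multiplied by 2.0 to 2.7 per SD lower month-3 score (logistic slopes 0.7 and 1.0).

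**3. Bias among completers.** If loss depends on the score at one visit and completers average *m* at that visit, they average ρ*m* at the other. The apparent change away from that visit is (ρ − 1)*m*.
- 14% loss: *m* is about 0.09 to 0.125, so the change is −0.4 × *m* = −0.04 to −0.05 SD.
- 28% loss: *m* is about 0.18 to 0.24, so the change is −0.07 to −0.10 SD.

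**4. False-positive rate.** The standard error of the paired change is √[2(1 − ρ)/n], with n the number of completers.
- 14% loss: n = 90 × 0.86 = 77.4; SE = √(0.8/77.4) = 0.102. Bias/SE is 0.04/0.102 = 0.39 to 0.05/0.102 = 0.49, giving about 7-8% by the normal approximation. Simulation gives about 7%.
- 28% loss: n = 90 × 0.72 = 64.8; SE = √(0.8/64.8) = 0.111. Bias/SE is 0.07/0.111 = 0.63 to 0.095/0.111 = 0.86, giving about 10-14%. Simulation gives 9-14%.

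**5. Direction.** A three-occasion simulation (100 women, correlation 0.5, 14% loss, a much steeper slope of 2 per SD) gave:

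| Loss depends on | Completers' apparent change | False positives |
|---|---|---|
| nothing | 0.00 | 4.6% |
| baseline score | −0.09 SD, baseline to month 6 | 13% |
| month-3 score | +0.10, then −0.10 SD | 14% |
| month-6 score | +0.09 SD, baseline to month 6 | 14% |
| overall level | 0.00 (all means +0.16 SD) | 4.9% |

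At 30% loss the three visit-specific rows rise to about 0.19 SD and 36-37%. The overall-level row stays at 0.00 and 4.6%.

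**6. What a likelihood model does with the same data** (two occasions, assumptions of step 2, 14-28% loss):

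| Loss depends on | Completers' bias | Mixed-model bias |
|---|---|---|
| month-3 score | −0.04 to −0.10 SD | about 0 |
| month-6 score (unseen) | +0.04 to +0.10 SD | +0.06 to +0.16 SD |
| overall level | 0.00 | +0.03 to +0.10 SD |

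**7. Precision.** With two occasions the two analyses have almost the same standard error (0.10 SD at 14% loss, 0.11 SD at 28%). With three occasions there is a cost. Assume random loss of 15% at month 3 and 25% at month 6, with correlation 0.6. The information per woman is the sum over response patterns of (pattern share) × (inverse covariance of the observed occasions). The completers' variance is 2(1 − ρ)/(share complete). The completers' standard error for baseline to month 6 is then about 3% larger if misses are nested (75% complete) and about 13% larger if they are independent (0.85 × 0.75 = 63.75% complete). The middle of that range is about 8%.

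**The case against.** **Losing women who do badly does not by itself create a change.** This stands. Completers are the same women at every occasion. If those with generally low quality of life leave, all means rise equally and the difference stays at zero. A reader might infer that any loss of women doing badly must appear as a false change, but the documents do not support that. They name return to use as a barrier without timing and without a stated link to a score at a given visit.

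**The error rate is not large at the loss seen so far.** This also stands. At 14% loss, under the moderate slopes, it is about 7%. Higher figures need more loss or a much steeper dependence, and neither is in the article. Relapsed women are still followed, and surveys do not require clinic or mentor visits, which should hold loss down.

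**A mixed model is not uniformly better.** This stands. A reader might take missing-at-random to be weaker than what the ANOVA needs. The two assumptions are not nested, and step 6 shows two plausible mechanisms in which the mixed model is more biased.

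**Missing-data rules belong in the full protocol or SAP.** This stands in part. The lack of a rule is not a fault of a condensed article, and completers-only handling is inferred from the method, not stated. But the method itself is stated, and in its classical form it carries that handling with it.

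**Conclusion.** The point holds in a limited form. The article fixes a method that, as classically applied, discards women with an incomplete set of surveys, while expecting loss partly related to how women are doing. The change can then be biased in either direction if loss depends on quality of life at a particular visit. It is not biased if loss depends only on overall level, although completers' means then sit above those of all consented women.

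Under loss driven by the month-3 score, the false-positive rate is about 7% at 14% loss and 9-14% at 28%. This rests on assumed values for the correlation, the slope, the number of women and the final loss. The 14% is an interim figure.

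The discrepancy over occasions is firmer, because it needs no assumptions. The analysis presumes a baseline score that Table 2 and the survey descriptions do not schedule. As scheduled, only a comparison of month 3 with month 6 is possible, with no pre-release reference.

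This is a minor point: one non-primary outcome in a single-group pilot, with no power claim attached.

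**What to change.** - Make the primary quality-of-life analysis a linear mixed model with occasion as a factor, unstructured covariance and REML, fitted to every available survey.
- Report how many women contribute at each occasion.
- Show the completers' result alongside, with a sensitivity analysis for scores missing not at random, since neither analysis is protected against every plausible mechanism.
- Reconcile the occasions: either add the WHOQOL-8 to the baseline survey and Table 2 for women still to be enrolled, or remove the baseline occasion from the analysis text.

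**Cost.** The change of model is wording only, with the same data and standard software; the sensitivity analysis is a small addition. The downside is reliance on missing-at-random given the observed scores. That differs from what the completers' analysis needs, and it can give more bias if loss follows overall level or the unseen month-6 score. With only two occasions the gain in precision is negligible. Adding a baseline measure would lengthen the baseline interview and would leave women already enrolled without a value.
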